## Interventions

### Mediterranean diet

Those allocated to one of the diet change groups will be required to record their estimate of their percentage adherence to the Mediterranean diet programme each day, with the goal of reaching and maintaining an 85 % adherence rate over the duration of the study. This programme has been produced in association with a specialist nutritional organisation, and includes a structured four week programme with meal ideas and recipes. Additionally, these participants will be supplied with a standard high-quality extra virgin olive oil to use for the duration of the trial.

### Exercise

While there are a number of types of exercise which are potentially cognitively beneficial, walking has been selected for this study. Regular walking, in particular, has been shown to have cognitive benefits in older cohorts [31, 32]. Additionally, walking does not require supervision or training from a health professional and may be suitable for frail elders or those with some functional limitations. For these reasons a walking program is deemed suitable for older participants and will be practical and cost effective to implement.

Those allocated to a group which includes exercise will be required to walk 4 to 5 times a week. They will follow a graduated program with the aim of walking at least 35–40 min as their aerobic exercise. Any participants who already walk this amount regularly will be asked to increase the amount of walking they do. Participants will be provided with pedometers and will be asked to record the number of minutes walked, distance travelled and the number of steps taken for each walking session.

## Procedure

Eligible participants will be assessed over four sessions at their living facility. An overview of these sessions is provided in the trial flow diagram (Fig. 1). During the first session, which takes place in the participant’s home, participants are screened for eligibility and assessed with the MMSE and the GDS. Eligible participants are requested to visit their doctor to obtain consent to participate and then to have blood taken for biomarker analysis. Session 2, conducted in a central treatment room in that participant’s living facility, is undertaken once doctor’s consent and blood biomarkers have been obtained. During this visit baseline assessment of all measures are undertaken and participants are informed of the group they have been randomly allocated to. The third session, an in home visit at the 3 month time point, will collect participant recorded diet and/or exercise data where appropriate, and any adherence issues will be discussed. Mood, exercise and sleep questionnaires will also be undertaken at this session. As shown in Fig. 1, the final session will be a full assessment visit, assessing all measures. This will be conducted in a central treatment room of the facility at the 6 month time point. Participant recorded exercise and diet data will also be collected during this session, enabling the investigators to estimate adherence to the intervention.

**Fig. 1 Fig1:**
[figure not shown]
LIILAC protocol flow diagram

## Primary outcome

The primary area of interest in this study is the effect of the dietary and exercise interventions on performance in a battery of cognitive measures. The Swinburne University Computerised Cognitive Assessment Battery (SUCCAB) will be undertaken at baseline and at 6 months post baseline. The SUCCAB has been used to assess cognitive performance in previous studies [15, 66, 68]. Reliability and validity assessment has demonstrated that SUCCAB is sensitive to ageing and correlates strongly with memory subtests in the WAIS-IV [15]. The primary outcome will be memory response time calculated as a composite measure from the SUCCAB memory sub-tests.

Additionally, the MMSE will be used to screen for dementia as well as assessing any global effects of the interventions after 6 months.

## Secondary outcomes

Potential mechanisms of action of improvement in cognition through changes in inflammation, glucoregulation, oxidative stress and more direct brain measures such as BDNF, will be examined.

The effects on mood, quality of life, cardiovascular function and overall perceived wellness in these cohorts will also be investigated as potential mechanisms by which exercise and dietary change may have an influence on cognition.

## Measures

Every participant in the study will undertake the same measures, regardless of the intervention they are assigned to.

### Screening

#### Mini Mental State Examination

Participants will be screened for cognitive impairment using the MMSE. Scores 24 or lower may indicate cognitive impairment. Participants scoring 24 or lower will not be eligible for participation.

#### Geriatric Depression Scale

The 30 item version of the GDS [69] will be used to ensure participants are free from depression as late onset depression can be associated with cognitive impairment. Participants scoring above 9 will not be eligible for participation.

### Cognitive assessment

#### Swinburne University Computerised Cognitive Assessment Battery

The SUCCAB is a validated computer based cognitive battery consisting of eight measures that were developed, based on cognitive and neuroimaging literature, to focus on cognitive domains that were most likely to decline with increasing age [15]. This battery uses a simple 5 button interface and has been validated in other studies involving the elderly [70, 71]. The eight measures of cognitive functioning assessed by the SUCCAB consist of Simple and Choice Reaction Times, Immediate and Delayed Recognition, Congruent and Incongruent Stroop colour-words, Spatial Working Memory and Contextual Memory. Computerised measures provide consistency in measurement across participants, and a more automated approach in analysis. The primary outcome will be a composite measure comprised of spatial working memory, immediate, delayed and contextual recognition response time. Secondary outcomes will be response time and accuracy on the individual SUCCAB measures, with the exception of the Congruent Stroop and Reaction Time tasks, as ceiling effects for accuracy are anticipated, response times will be the sole outcome for these tasks.

### Cardiovascular assessment

The effect of the intervention on cardiovascular factors will focus on peripheral and central blood pressures as well as arterial stiffness. These measures will be conducted using applanation tonometry with the SphygmoCor XCEL system. Aortic blood pressure and pulse pressure will be derived automatically, via a brachial blood pressure cuff. Standard brachial blood pressure will also be measured during this process, using an average taken over three recordings. Pulse wave velocity will be derived using a femoral cuff to capture the femoral waveform and tonometer pressure sensor to capture the carotid waveform.

### Biomarker assessment

The blood tests to be undertaken are: BDNF, Cholesterol, Triglycerides, Liver Function Test (LFT), Glucose, Urea, C-Reactive Protein (CRP), Red Cell Folate, Homocysteine, Haemoglobin A1c (HbA1c), Insulin-Like Growth Factor 1 (IGF-1/Somatomedin C) and Vitamins B6, B12 and D. Participants will be asked to fast before these blood tests.

Bloods will be taken by a commercial pathology company or the participant’s medical practitioner. The blood assessment, with the exception of BDNF, is in accordance with a regular medical assessment and represents fairly standard 6 month monitoring conducted by the residents’ medical practitioners.

### Mood and wellness assessment

#### Depression Anxiety Stress Scale (DASS), Profile of Mood States (POMS) and General Health Questionnaire (GHQ)

These self-report mood scales will be used to assess changes in mood across the study. The DASS measures the three related negative emotional states of depression, anxiety and stress [72]. The POMS used to assess transient, fluctuating feelings and enduring affect states allowing participants to report their mood over the past week [73]. The GHQ comprises 60 items and assesses changes in the ability to carry out normal daily functions, somatic symptoms and insomnia, and feelings of anxiety and depression [74].

#### Perceived Wellness Survey

The perceived wellness survey is a set of statements that are designed to provide information about a person’s wellness perceptions [75].

#### Sleep assessment

This study will include the Pittsburgh Sleep Quality Index [76]. This measure assesses ‘components’ of sleep such as disturbances, latency, duration, efficiency, use of sleep medication and daytime dysfunction.

### Dietary assessment

#### Mediterranean diet scale

Adherence to the Mediterranean diet will be assessed by a 10-point Mediterranean-diet scale that incorporated the salient characteristics of this diet. Scores range from 0 to 9, with higher scores indicating greater adherence [77].

#### Food frequency assessment

The Cancer Council Food Frequency Questionnaire [78] will be used to collect additional dietary information. They will also form the basis for nutritional evaluation and to assess adherence to the Mediterranean Diet.

### Exercise assessment

#### The 6 min walk test

The 6 min Walk test will be utilised to indicate baseline fitness as well as improvement in fitness over the study [79]. In this assessment participants will between two markers placed 10 m apart. The objective of this test is to walk for as far as possible in 6 min.

#### Borg assessment

The Modified Borg Scale [80] will be used to rate degree of breathlessness and/or difficult, uncomfortable or laboured breathing as well as fatigue level. Participants will complete the Borg Scale after their 6 min walk test.

#### Community Healthy Activities Model Program for Seniors (CHAMPS) questionnaire

The CHAMPS will be used to the assess baseline physical activity of participants [81]. It will also form part of the assessment of change in overall physical activity across the duration of the trial.

### Demographic and morphometric measures

Age, gender, education and smoking status will be recorded at the commencement of the study. Height, weight, hip and waist circumference will be assessed at baseline and the six month time point, while medication and nutritional supplement information will be collected at all three time points. Additionally, information regarding personal and first degree relative (parents, siblings and children) history of cardiac, stroke or dementia issues will also be recorded.

## Analysis

### Primary outcome

The primary outcome will be response time on the SUCCAB memory measures. Previously benefits to response time on SUCCAB memory measures has been demonstrated following multivitamin [67] and other nutraceutical intervention [68]. Mixed design, repeated measures analysis of co-variance (ANCOVA) will be used to assess treatment-related changes in cognitive performance over the study. Relevant covariates may include group differences in cognitive performance or biomarkers at baseline and co-habitation of participants, where couples are taking part in the intervention trial.

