## Participants

In total, 148 participants who live independently in aged care facilities across a minimum of 15 sites, and who are aged between 60 and 90 years, will participate in this study. These residents live in their own unit or similar accommodation, and are generally physically and mentally capable of caring for themselves in all aspects of daily living. The independent aged care resident population was selected due the generally greater homogeneity of the population and living conditions than that found in the broader community. Furthermore, by focusing on independent living in aged care facilities, this research aims to examine the efficacy of programs aimed at minimising cognitive decline and reducing the rate of transfer to low and high care accommodation.

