## Sample size

To date no studies using specific measures of cognition more sensitive than the MMSE have investigated the cognitive effects of a Mediterranean dietary intervention in the elderly. However, numerous trials have examined the effects of exercise fitness interventions. In a meta-analysis conducted to investigate the potential for fitness training to improve cognition in sedentary, but otherwise healthy, older adults, fitness training increased cognitive performance 0.5 SD on average, regardless of the type of cognitive task or the training method [27]. Using Cohen’s effect size criteria, this represents a medium effect size [65]. Although there are no relevant trials which have focussed on the Mediterranean diet, from which to determine an effect size, we have previously identified slightly larger effect sizes on SUCCAB memory measures following several months combined micronutrient, mineral and herbal supplementation in older people with risk factors for cognitive decline [66, 67]. We would anticipate the dietary change condition may exert many of the same benefits as micronutrient dietary supplementation, therefore a comparable effect size may be anticipated. Power analysis was conducted using GPower 3.1.3 to determine the sample size required for a four armed intervention (exercise change only, diet change only, exercise and diet change, no change) using an analysis of variance (ANOVA) design. It was indicated that a total sample of 128 participants would be required to detect a moderate effect size (*f* = 0.30), power of 80 % and a significance level of 5 %. Based on previous trials conducted by the Swinburne University Centre for Human Psychopharmacology, an allowance for a 15 % drop out from the trial has been factored in. Therefore, a total sample of 148 participants will be recruited for this trial, with 37 individuals randomised to each arm of the study.

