### Secondary outcomes

All other cognitive, biomarker, mood, wellness and exercise measures will be treated as secondary outcomes. Mixed design, repeated measures analysis of covariance (ANCOVA) will be used to assess treatment-related changes in all secondary outcomes over the study. Hierarchical regression will be used to establish the relationship between change in biomarkers and changes in cognitive function. Secondary analysis will examine the pooled effects of the two intervention arms involving the Mediterranean diet versus the control arm and the two intervention arms involving exercise versus the control arm.

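### The repeated-measures ANCOVA named for every outcome is in its usual form a completers' analysis: baseline adjustment is left optional for the primary score, and collected data are discarded for the three-visit questionnaires

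*Protocol article*

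**What the plan says.** - Analysis, Primary outcome: "Mixed design, repeated measures analysis of co-variance (ANCOVA) will be used to assess treatment-related changes in cognitive performance over the study". The covariates are listed as possibilities, not commitments. Baseline group differences in cognition or biomarkers are among them.
- Analysis, Secondary outcomes: "Mixed design, repeated measures analysis of covariance (ANCOVA) will be used to assess treatment-related changes in all secondary outcomes over the study".
- Primary outcome: the SUCCAB, source of the memory response-time composite, is given at baseline and at 6 months, with no measurement in between.
- Procedure: the 6-month session assesses all measures. Of the 3-month session it says "Mood, exercise and sleep questionnaires will also be undertaken at this session", so those questionnaires have three time points.
- Sample size: "an allowance for a 15 % drop out from the trial has been factored in", and therefore "a total sample of 148 participants will be recruited for this trial, with 37 individuals randomised to each arm of the study".

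The article names no likelihood-based or multilevel model.

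**The concern.** A mixed-design repeated-measures ANCOVA is the classical between-within model. As normally fitted, it needs a complete set of repeated measures, and of any covariates, for each person. This has two consequences.

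1. **Primary composite.** With two visits, the group-by-time test is a comparison of mean change between arms among those who attended both. The trial is unblinded, and three of its four arms ask for a six-month change in diet, walking or both, so retention could plausibly differ by arm in amount or in kind. If slower people leave one arm more readily than another, completers start from different baselines. Regression to the mean then appears as a treatment difference.
2. **Three-visit questionnaires.** Someone who misses only month 3 is removed although baseline and month 6 are in hand. Someone who misses only month 6 is removed although baseline and month 3 are in hand.

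At stake are the comparison of all randomised participants and, for the second group of outcomes, precision already paid for.

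**Working it through.** **Inputs from the article.** 148 recruited, 37 per arm, 15% dropout allowance, 128 needed for a four-arm ANOVA at *f* = 0.30, 80% power and 5% significance; a cited average exercise effect of 0.5 SD.

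**Assumptions, not in the article.** Correlation between visits; how dropout relates to baseline; 8% missing month 3.

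**Step 1: the plan's own figure.** One-way ANOVA, 4 groups, noncentral F with 3 and N − 4 degrees of freedom and noncentrality N × 0.30². The smallest N with 80% power is 126; rounded up to equal arms it is 128 (power 0.810). So 128 reproduces. Then 128 × 1.15 = 147.2, which gives 148 when rounded up to equal arms.

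**Step 2: who is left.** 148 × 0.15 = 22.2, so about 22 people have no 6-month composite if the allowance is used in full. 148 × 0.85 = 125.8 remain, 31.45 per arm. Power at N = 126 is 0.803. The loss is budgeted for; the remaining question is bias.

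**Step 3: bias of the completers' change contrast.** Standardise both visits to SD 1 with correlation ρ and no treatment effect. Let 15% drop out of each arm, unrelated to baseline in control but with log-odds γ per SD of slower baseline in one lifestyle arm. If m is the completers' mean baseline in that arm, their mean change is ρm − m, so the bias is (ρ − 1) × m. Numerical integration gives m:

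| γ | m | bias at ρ = 0.5 | bias at ρ = 0.8 |
|---|---|---|---|
| 0.5 | −0.073 | 0.036 SD | 0.015 SD |
| 1.0 | −0.133 | 0.066 SD | 0.027 SD |
| 1.5 | −0.175 | 0.088 SD | 0.035 SD |

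The standard error of the contrast is √(2 × 2(1 − ρ) / 31.45), which is 0.25 at ρ = 0.5 and 0.16 at ρ = 0.8. The largest bias is 0.088 / 0.25, about a third of a standard error, and 0.088 / 0.5, about 18% of the cited effect. In this pattern it makes the lifestyle arm look slower; the opposite pattern reverses the sign.

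**Step 4: what removes it.** A likelihood model with baseline as a response estimates the arm's month-6 mean as ρm + ρ(0 − m) = 0, so the change is unbiased. Completer ANCOVA with baseline score as a covariate does the same: simulated with 2 million people per arm, its absolute bias was at most 0.002 SD in all six cells.

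**Step 5: three-visit outcomes.** With 15% missing month 6 and an assumed 8% missing month 3, complete rows number 148 × 0.85 × 0.92 = 115.7. Simulating four arms of 37 with correlation 0.6 (1,500 runs) gave a standard error for the month-6 change contrast of 0.232 SD with listwise deletion and 0.219 SD by maximum likelihood with unstructured covariance. The variance ratio is (0.232 / 0.219)² = 1.12, and 1 − 1/1.12 = 0.11, about one participant in nine. A repeat simulation gave 0.237 against 0.224, again a ratio of 1.12.

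**The case against.** **The bias assumes an unadjusted contrast, although the article names an analysis of covariance and lists baseline cognition as a candidate covariate.** This is largely right: with baseline score in the model, the bias in Step 3 disappears without any change of method. What remains is that the covariate is optional, so the stated plan does not secure that protection.

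**A mixed model recovers no missing 6-month SUCCAB score.** Also right. With one post-baseline measurement it makes the same missing-at-random assumption as baseline-adjusted ANCOVA and adds little precision. Its gain for the primary outcome is limited to removing baseline-dependent bias.

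**The article never says complete cases, and missing-data handling belongs in the SAP.** No imputation section is being asked for here. The point concerns the method the article does fix, whose usual form needs complete rows. A SAP not shown could run it on imputed data, and that would meet part of the concern.

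**Stronger readings that the document does not support.**
- A reader might infer that the trial is underpowered by these losses. It is not; the recruited number allows for them.
- A reader might take 15% as the expected rate of missed 6-month sessions. It is a planning allowance for dropout.
- A reader might infer that people moving to higher care will be lost. The Participants section mentions "minimising cognitive decline and reducing the rate of transfer to low and high care accommodation" as an aim of the research; nothing says that such people withdraw or go unassessed.
- Dropout that differs by arm is plausible in an unblinded lifestyle trial, but the article does not state it.

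**Conclusion.** The concern stands in a limited form. The method fixed for every outcome is, as usually fitted, an analysis of completers.

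- **Primary composite:** possible bias of about 0.01 to 0.09 SD, conditional on dropout that depends on baseline score in one arm but not in control, 15% dropout per arm and a correlation of 0.5 to 0.8. It is close to zero if baseline score is always in the model, which the article does not guarantee. Dropout that depends on the unseen 6-month score would not be cured by either method.
- **Three-visit questionnaires:** about 12% more variance than a likelihood analysis of the same data, resting on the assumed 8% missing month 3 and correlation 0.6. These are secondary outcomes and the loss is modest.

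The change is worth making because it is cheap and better than the stated method, not because the trial's result is otherwise in doubt.

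**What to change.** In both Analysis paragraphs (Primary outcome and Secondary outcomes), replace the repeated-measures ANCOVA with a likelihood-based linear mixed model for repeated measures:

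- every randomised participant, in the assigned arm;
- all available visits as responses (baseline, month 3 where measured, month 6), so that baseline is always in the model;
- categorical visit, arm-by-visit terms and an unstructured within-person covariance;
- the month-6 arm-versus-control contrast named as the treatment effect.

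State that the primary result relies on missing at random. As an optional addition, repeat the primary analysis with the missing 6-month scores in the lifestyle arms shifted over a fixed range, for example 0 to 0.5 SD slower, and report where the conclusion changes.

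The cost is a rewording of two paragraphs and slightly more analysis work in standard software. It needs no new participants, visits or measures. The downside is an explicit missing-at-random assumption, which the optional sensitivity analysis would probe.

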## Design and methodology

### Design

This is a randomised, controlled, four-arm parallel groups design. However, given the nature of the interventions, this study is not blinded as both investigators and participants will clearly know what the intervention is, as participants in the lifestyle arms will be actively working towards maintaining the lifestyle change. Participants will be randomly allocated to one of the following four groups:ControlExercise interventionDietary interventionCombined dietary and exercise intervention

The randomisation sequence will be created by permuting into blocks of 4. While allocation of participants to these groups will be randomised, for reasons of practicality, and to avoid cross contamination between the requirements of each group, when cohabiting couples participate, one person will be randomly allocated to a group and the other will be allocated to the same group.

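### Cohabiting couples are allocated as a unit, but the stated sample size and analysis do not provide for within-couple correlation, so the 5% level and 80% power are not assured

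*Protocol article*

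**What the plan says.** Four statements in the protocol article bear on this.

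- **Design.** When a cohabiting couple takes part, "one person will be randomly allocated to a group and the other will be allocated to the same group". The reasons given are practicality and avoiding contamination between arms.
- **Sample size.** The calculation was made "using an analysis of variance (ANOVA) design". It gives 128 participants "to detect a moderate effect size" (f = 0.30), with "power of 80 % and a significance level of 5"%. A 15% dropout allowance takes this to 148, "with 37 individuals randomised to each arm of the study". No design effect for couples appears.
- **Analysis, Primary outcome.** "Mixed design, repeated measures analysis of co-variance (ANCOVA) will be used to assess treatment-related changes in cognitive performance over the study". On couples it adds only that the covariates may include "co-habitation of participants, where couples are taking part in the intervention trial".
- **Analysis, Secondary outcomes.** The same type of model is used for all secondary outcomes, with no further provision for couples.

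**The concern.** The second member of a couple is not randomised, so for couples the household is the unit of allocation. The protocol keeps partners together because their behaviour would otherwise mix across arms. That influence is also a plausible source of correlation in how partners respond.

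The sample size treats everyone as independently randomised. The named analysis gives couples an optional covariate and mentions no household random effect, GEE or clustered standard error. A co-habitation indicator estimates a mean difference between people in couples and people living alone. It does not affect the covariance between two partners' residuals.

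At stake is the validity of the between-arm p-values and confidence intervals, first for the memory response-time composite and then for the secondary outcomes. Also at stake is whether 80% power is available to an analysis that handles couples properly.

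**Working it through.** **1. The protocol's own figure.** Inputs from the Sample size section are 4 groups, f = 0.30, alpha 5% and power 80%. Power is P(F′ > F crit), where F′ is noncentral F with 3 and N − 4 degrees of freedom and noncentrality λ = N·f².

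- N = 125 gives 79.96% and N = 126 gives 80.3%, so the minimum is 126.
- With equal arms this becomes 128, with power 81.0%. The stated 128 reproduces.
- 128 × 1.15 = 147.2, which becomes 148 in four arms of 37.
- After 15% loss, 148 × 0.85 = 125.8, or about 126 completers. Power is then 80.3%, so there is almost no room for a design effect.

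**2. Design effect.** Let s be the share of participants in couples and ρ the within-couple correlation of the analysed quantity. An arm of n people contains sn/2 couples, and each adds 2ρσ² to the variance of the arm total. So

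Var(total) = nσ² + (sn/2)·2ρσ² = nσ²(1 + sρ), and DE = 1 + sρ.

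**3. Consequences.** The protocol gives neither s nor ρ, so the values below are assumptions.

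- Type I error of the unadjusted test at N = 128 is approximately P(F(3,124) > 2.678/DE).
- Power of a test that respects couples is the noncentral F power at an effective N of 126/DE.

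| s | ρ | DE | Type I error | Effective N | Power |
|---|---|---|---|---|---|
| 0.10 | 0.1 | 1.01 | 5.2% | 124.8 | 79.9% |
| 0.20 | 0.1 | 1.02 | 5.3% | 123.5 | 79.4% |
| 0.20 | 0.3 | 1.06 | 6.1% | 118.9 | 77.6% |
| 0.50 | 0.2 | 1.10 | 6.8% | 114.5 | 75.9% |
| 0.50 | 0.3 | 1.15 | 7.8% | 109.6 | 73.7% |
| 0.50 | 0.5 | 1.25 | 9.8% | 100.8 | 69.6% |

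**4. Does the covariate help?** A simulation used 32 per arm and 20,000 trials per setting, testing arm with and without a fixed co-habitation indicator. With half of participants in couples, type I error was:

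- ρ = 0.2: 6.7% without the indicator, 6.9% with it.
- ρ = 0.5: 10.0% without, 10.1% with.

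The indicator makes no material difference.

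**5. Which correlation counts?** The planned analysis concerns change. With two time points, the group-by-time test is a test on the difference, so similarity between partners that is stable over time cancels. Simulating the change contrast with half of participants in couples and a level correlation of 0.5, type I error is about 5% if changes are uncorrelated and about 10% if changes correlate at 0.5. In the table, therefore, ρ is the correlation of change, or of the baseline-adjusted 6-month outcome.

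**The case against.** The strongest case against is that the documents cannot tell a negligible problem from a material one. They give no share of couples and no correlation. With 10–20% in couples and ρ = 0.1, type I error is 5.2–5.3% and power is within about one percentage point of 80%. A reader might infer that the trial fails to deliver its 5% level and 80% power. The documents do not support that statement, because both figures depend on quantities they do not give.

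Three further objections stand in part.

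- **Partners can be alike without harm.** Similarity in level largely drops out of a change analysis, so a high correlation in raw scores is no evidence of inflation. If baseline is instead a covariate, part of the level correlation can remain. Shared meals and walking could also correlate the changes themselves.
- **The planned test does not itself lose rejections.** In simulation the uncorrected test still rejected about 80–81% of the time at f = 0.30. The power shortfall belongs to a valid clustered test.
- **Independence is inferred.** The article never says that partners will be analysed as independent, it does recognise co-habitation, and it does not define the covariate's form. Error structure is also often left to the SAP.

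The last objection does not remove the point. The article names a device for couples, it is optional, and neither obvious form of it works. An indicator leaves the correlation in place. Couple identity as a fixed factor is nested within arm, so couples would contribute nothing to the arm comparison.

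**Conclusion.** The point holds in conditional form. Couples are allocated together, the sample size carries no design effect, and the one stated provision does not model within-couple correlation. If partners' changes or baseline-adjusted outcomes are positively correlated, the planned between-arm standard errors are too small and the 5% level is not assured. A valid clustered analysis then falls below 80% power, because only about 126 completers are expected and 126 is the minimum. The shortfall is trivial if couples are few or the correlation is low.

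Over the assumed range of 10–50% in couples and ρ from 0.1 to 0.5, type I error runs from about 5.2% to 9.8%, and clustered power from about 80% to 70%. These figures use the omnibus F test on which the protocol was sized and a large-sample design effect.

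**What to change.** For the primary and secondary models, prespecify one of the following, with participants not in a couple as households of size one:

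- household-clustered standard errors;
- a household random effect in a model of the 6-month outcome adjusted for baseline;
- a household-by-time effect in the repeated-measures model.

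A household random intercept alone in the two-time-point model is not enough. It absorbs shared level, which already cancels from the change contrast, and leaves shared change unmodelled. Co-habitation may stay as a covariate if it is thought prognostic, but not as the means of handling clustering.

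In the Sample size section, state that couples are allocated as a unit, give an expected share and a range for the correlation, and restate power with a design effect of 1 + share × ICC. This does not require enrolling more participants.

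The change is to wording and model specification only, since couples must already be identified to be allocated together. The price is slightly wider intervals and a slightly lower stated power. If couples prove rare, the results will barely move.
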